## Abstract

**Introduction:**

Idiopathic nephrotic syndrome (INS) is characterised by a high relapse rate up to 80% after initial response to standard therapy with corticosteroids. Steroid toxicity is common and causes a great burden of disease that negatively influences the health-related quality of life (HRQoL). Recently, studies have shown that levamisole, an anthelminthic drug, significantly improves relapse-free survival in children with frequent relapses or steroid dependency. Compared with other steroid-sparing drugs, levamisole has relatively few side effects. We hypothesise that adding levamisole to standard therapy with corticosteroids in children with a first episode of INS will prevent relapses, decrease cumulative dosage of steroids used and improve HRQoL. This paper presents the study protocol for the LEARNS study (LEvamisole as Adjuvant therapy to Reduce relapses of Nephrotic Syndrome).

**Methods and analysis:**

An international, double-blind, placebo-controlled randomised trial will be conducted in 20 participating hospitals in the Netherlands and Belgium. Participants (n=92) with a first episode of INS, aged 2–16 years, who achieve remission after 4 weeks of oral prednisolone will be randomly assigned (1:1) to receive either levamisole 2.5 mg/kg alternate day or placebo added to prednisolone (18-week tapering schedule) for a total of 24 weeks. Follow-up will be until 2 years after first presentation. Additionally, parents and/or children will fill out five HRQoL questionnaires. Primary outcome of the LEARNS study is occurrence of relapses within 12 months after first presentation. Secondary outcomes include time to first relapse, cumulative steroid dose after 2 years, safety parameters and quality of life scores.

**Ethics and dissemination:**

The trial was approved by the Medical Ethical Committee. Results of the study will be published in a peer-reviewed journal.

**Trial registration number:**

NL6826, 2017-001025-41

Strengths and limitations of this studyInvestigator-initiated, multicentre, double-blind, randomised, placebo-controlled study.Additional study on health-related quality of life.Homogenous patient population.Possibility to pool data with similar ongoing trial (Nephrovir-3).Sample size only powered on primary outcome (ie, not for subgroup analyses).

## Background

Idiopathic nephrotic syndrome (INS) is a rare disease that predominantly affects young children. In the Netherlands, the yearly incidence is 1.52 per 100 000 children (an estimated 60 new cases per year).^1^ INS is characterised by proteinuria, hypoalbuminaemia and oedema. It is often accompanied by hyperlipidaemia. Initial treatment consists of 8–20 weeks of corticosteroids, of which at least 4 weeks single-daily dose of 60 mg/m^2^ followed by an alternate schedule.^2^ The vast majority of patients shows remission within 4 weeks, after which the diagnosis minimal change disease is assumed and no kidney biopsy is indicated.^3^ Unfortunately, 80% of the responders experience at least one relapse; half of those patients experiencing frequent relapses (FRNS) or becoming steroid-dependent (SDNS).^4^ Relapses are further treated with steroids; however, steroids are associated with many side effects.^5^ In these cases, steroid-sparing drugs are recommended.^2^ These include cyclophosphamide, calcineurin inhibitors, mycophenolate mofetil (MMF) and rituximab. But still, all come with substantial toxicity. A promising steroid-sparing agent is levamisole, an anthelminthic drug mostly used in a veterinary setting. Levamisole is, contrary to other steroid-sparing drugs, not an immunosuppressant, but acts as an immunomodulator. It has relatively few side effects of which neutropenia is the most serious and most common that requires frequent check-ups. Recent trials show a beneficial effect of adjuvant treatment with levamisole to corticosteroids in children with FRNS or SDNS, but also that treatment is safe.^6–8^

In order to prevent the frequency of relapses, several steroid schedules for the treatment of the first episode of INS have been studied, for instance, comparing a longer with a shorter course.^4^ To our knowledge, no trials have been performed investigating the efficacy of levamisole as an adjuvant agent to initial steroid treatment on preventing relapses. Currently, a study similar to ours is underway in France (Nephrovir-3).

We hypothesise that adding levamisole to standard steroid treatment in children with a first episode of INS will prevent relapses. This is substantiated by the fact that (1) INS is characterised by a T helper cell (Th) type 2 (antibody-mediated) immune response, and that (2) levamisole is able to skew the Th type 2 response into a Th type 1 (cell-mediated) response,^9 10^ and thus, restoring the balance. The aim of the LEARNS study is to investigate the efficacy and safety of adjuvant levamisole in children with a first episode of INS by conducting a randomised, double-blind, placebo-controlled clinical trial in 20 hospitals in the Netherlands and Belgium. The trial is extended with a sub-study on the health-related quality of life (HRQoL).

## Methods and analysis

### Study design

The LEARNS study is an international, phase 3, double-blind, parallel, two-arm, randomised, placebo-controlled superiority trial. The study is coordinated by the Amsterdam University Medical Centers, University of Amsterdam and is conducted in 15 and 5 participating centres in the Netherlands and Belgium, respectively. Local investigators are paediatric nephrologists or paediatricians with a special interest in paediatric nephrology in both university and local hospitals. Together, the participating sites cover a large geographical area. The expected total duration of the study is 4 years, consisting of 2 years of inclusion and 2 years of follow-up since first presentation (figure 1).

**Figure 1 F1:**
[figure not shown]
Schematic overview of study design. AD, alternate days.

### Objectives

The primary objective of the study is to investigate the effect of additional levamisole to standard steroid therapy in comparison with placebo from 4 to 28 weeks (figure 1) after the start of the first episode of steroid-sensitive INS (SSNS) in children (age 2–16 years) on the occurrence of any relapse within 12 months after first presentation.

Secondary objectives are:To investigate differences between the two study groups in time to first relapse, the number of relapses, cumulative steroid dosage and the occurrence of SDNS and FRNS in a 2-year period.To investigate HRQoL, psychosocial adjustment, parental distress at different stages of treatment (longitudinal and cross-sectional) and to identify medical and personal factors related to HRQoL.To investigate the consequences of the disease on days of missing school for children, (financial) problems for parents, outpatient visits and hospital admissions.

### Population

Children between 2 and 16 years of age who present with a first episode of INS will be screened for eligibility. Those who achieve remission within 4 weeks of oral treatment with corticosteroids will be screened for inclusion in the randomised controlled trial (RCT). Remission is defined as the absence of proteinuria for three consecutive days, confirmed by quantitative urinalysis (protein–creatinine ratio <20 mg/mmol creatinine). All inclusion and exclusion criteria are described in box 1. SSNS will be defined according to current guidelines.^2^
Box 1Inclusion and exclusion criteria for participation in the randomised controlled trialInclusion criteriaFirst episode of steroid-sensitive INS, as defined by:Proteinuria (>200 mg/mmol creatinine).Hypoalbuminaemia (<25 g/L).Oedema.Remission, defined by:Absence of proteinuria (<20 mg/mmol creatinine) for three consecutive days within 4 weeks of steroid treatment.Complement C3 within normal range.Age 2–16 years.Written informed consent.Weight >9 kg.Ability to swallow 5 mg (placebo) tablet (successful swallowing test in children<6 years).Negative pregnancy test in girls who are of childbearing potential.Absence of contraindication for levamisole use, defined as neutropenia (<1500/mm^3^).Exclusion criteriaPrevious episode(s) of INS.Steroid-resistant INS, defined by:Persistent proteinuria at 4 weeks after start steroid treatment.Previous or current malignancy, diabetes mellitus, current liver disease or epileptic convulsions.Hypersensitivity to levamisole or one of its substances (lactose).Inability to comply with the study protocol.

### Intervention

After confirming the diagnosis of INS, all patients will be treated with oral prednisolone according to the French protocol, which is an 18-week tapering schedule (figure 1).^11^ In addition to prednisolone, all patients will receive vitamin D (400 IE/day for children <12 years; 800 IE/day for children ≥12 years). When participating in the trial, concomitant use of any immunosuppressive and/or stimulant medication other than prednisolone is prohibited. Because of their anti-proteinuric actions, non-steroid anti-inflammatory drugs, ACE-inhibitors and angiotensin II-receptor blockers are prohibited as well. If remission is achieved at week 4, study subjects will receive 2.5 mg/kg levamisole or placebo on alternate days for a total of 24 weeks (figure 1). The current dosage schedule has been established in a previous study.^12^ The dose of the study medication is calculated based on the patient’s weight, with a maximum of 150 mg/dose. Prednisolone and study medication need to be taken simultaneously. A missed dose can be taken within 24 hours of scheduled time. After 24 hours or more, the dose will not be taken and the next dose will be as scheduled. Study treatment will be (temporarily) stopped in case of the following situations: relapse, neutropenia <500/mm^3^, elevated liver enzymes >5× upper limit of normal, at the patient’s and/or their parent’s request, and/or withdrawal of informed consent. More details of temporarily stopping the study medication in case of moderate to mild neutropenia can be found in the online supplement 1. In case of a relapse, treatment will be determined by the treating physician, but generally consists of daily prednisolone (60 mg/m^2^) until remission, followed by 40 mg/m^2^ every other day for 6 weeks.

10.1136/bmjopen-2018-027011.supp1Supplementary data

When using study medication, patients will have regular check-ups for monitoring disease activity and adverse events (table 1). Adverse events are defined by any undesirable event that occurs after inclusion until 30 days after stopping study medication.

**Table 1 T1:** Overview of study visits. All assessments at week 0 are part of standard of care

Visit	0	R1	2	3	4	5		6	7	8	9	Relapse	EoS
Week	0	4	8	12	16	20		28	36	44	52		104
Informed consent		X											
Entry criteria	X	X											
Medical history	X	X											
Physical examination	X	X	X	X	X	X		X	X	X	X	X	X
Laboratory examination	X	X	X	X	X	X		X	X	X	X	X	(X)
(Serious) adverse events		X	X	X	X	X		X	X				
Prednisolone													
Study medication													
Quality of life	X	X						X			X		X
Drug dispensing		X			X								
Drug accountability					X			X					

The colour shades indicate in which period prednisolone and study medication is used.

EoS, end of study; R, randomisation; (X), if indicated by treating physician.

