### Study endpoints

The primary endpoint of the study is the occurrence of a first relapse within 12 months (week 52) after first presentation. Relapse is defined as having proteinuria (3+ on urine dipstick confirmed by >200 mg/mmol creatinine on quantitative urinalysis) for three consecutive days.

Secondary endpoints can be found in box 2.Box 2Secondary endpoints are being compared between the intervention groupsTime to first relapse (days).Relapse rate over 2-year period (n/year).Cumulative steroid dose over 2-year period (mg/m^2^).Number of (serious) adverse events (n).Number of treatment discontinuations (n).Proportion patients with FRNS or SDNS (%).Days of missing school (days), outpatient visits (n), hospitalisation days (days).HRQoL and psychosocial adaptation at different time points (see table 1):Cross-sectional and longitudinal.Comparison with healthy peers and other chronic diseases.FRNS, frequent relapsing nephrotic syndrome; HRQoL, health-related quality of life; SDNS, steroid-dependent nephrotic syndrome.

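### Adverse-event counting ends 30 days after study drug stops and relapse is a listed reason to stop, so unless drug is resumed the two arms are observed for unequal time; the rule also conflicts with Table 1 for children who stop early

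*Protocol article*

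**What the plan says.** All of this is in the protocol article.

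- **Intervention, end of counting.** "Adverse events are defined by any undesirable event that occurs after inclusion until 30 days after stopping study medication".
- **Intervention, planned exposure.** If in remission at week 4, "study subjects will receive 2.5 mg/kg levamisole or placebo on alternate days for a total of 24 weeks", that is, to week 28.
- **Intervention, reasons to stop.** "Study treatment will be (temporarily) stopped in case of the following situations: relapse, neutropenia" below a threshold, raised liver enzymes, request, or withdrawal of consent. The supplement is cited only for temporary stops in moderate to mild neutropenia. The article does not say whether or when study drug is resumed after a relapse.
- **Intervention, relapse treatment.** It is left to the treating physician but "generally consists of daily prednisolone (60 mg/m^2^) until remission, followed by 40 mg/m^2^ every other day for 6 weeks".
- **Table 1.** The adverse-event row is ticked at weeks 4, 8, 12, 16, 20, 28 and 36. It is not ticked at weeks 44, 52 or 104, or in the relapse column.
- **Study endpoints, Box 2.** Both "Number of (serious) adverse events (n" and "Number of treatment discontinuations (n" are compared between arms as counts. Discontinuation is not defined. Cumulative steroid dose is compared over 2 years.
- **Statistical analysis.** The safety population is as treated. The between-group comparisons named are the t-test, Mann-Whitney and χ² tests, none of which allows for unequal observation time.

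**The concern.** The period over which a child's adverse events count depends on when that child stops study drug, and one reason for stopping is the event the drug is meant to prevent. If levamisole works and relapse ends dosing, placebo children leave the counting window sooner. A raw count would then show more events on levamisole even if the drug caused none.

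The window also cuts off part of the harm that motivates the trial. The usual relapse steroid course lasts longer than 30 days, and a relapse well after week 28 falls outside the window altogether.

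The Intervention section and Table 1 also point to different end dates for a child who stops early, so sites could apply either. Events that were never collected cannot be recovered by any later analysis plan.

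**Working it through.** **Inputs.** From Sample size: relapse within 12 months 75% (placebo) and 45% (levamisole), 5% two-sided, 80% power, 10% drop-out, 92 children. From Randomisation: 1:1, so 46 per arm. From Intervention: drug from week 4 to week 28, then 30 days = 30/7 = 4.29 weeks.

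**The plan's own figure.** With pooled variance and no continuity correction, n = [1.960·√(2·0.60·0.40) + 0.842·√(0.75·0.25 + 0.45·0.55)]² / 0.30² = 40.7, so 41 per arm (power 80.3%). Then 82/0.9 = 91.1, so 92. The sample size reproduces and is not in dispute; it is used only for the relapse rates.

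**Window length if a relapse stop is permanent.** Let relapse have constant hazard λ from week s to week 52, with λ = −ln(1 − p)/(52 − s). Then:

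- P(relapse on drug) = 1 − exp(−λ(28 − s))
- mean weeks on drug = (s − 4) + P/λ
- mean window = mean weeks on drug + 4.29

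The article gives no relapse timing, so two assumptions bracket it. The second takes the 18-week prednisolone schedule as ending 18 weeks after presentation, with no relapse before then.

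| | Placebo | Levamisole |
|---|---|---|
| **s = 4:** λ per week | 0.02888 | 0.01245 |
| P(relapse on drug) | 50% | 26% |
| Relapse stops of 46 | 23.0 | 11.9 |
| Mean window, weeks | 17.31 + 4.29 = 21.6 | 20.75 + 4.29 = 25.0 |
| **s = 18:** λ per week | 0.04077 | 0.01758 |
| P(relapse on drug) | 33% | 16% |
| Relapse stops of 46 | 15.4 | 7.4 |
| Mean window, weeks | 22.21 + 4.29 = 26.5 | 23.17 + 4.29 = 27.5 |

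A child who completes treatment has 24 + 4.29 = 28.3 weeks.

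At the same event rate per week in both arms, the ratio of expected counts (levamisole to placebo) is 25.03/21.60 = 1.16 for s = 4 and 27.46/26.50 = 1.04 for s = 18. A cruder check, with 25% to 75% of the 12-month relapses falling evenly over the time on drug, gives a levamisole window 3.5% to 12.5% longer.

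**What could offset it.** Suppose the event rate in the 30 days after a relapse stop is k times the rate elsewhere. The counts are equal when (k − 1) × 4.29 × (difference in P) = difference in mean window:

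- s = 4: k = 1 + 3.43/(4.29 × 0.242) = 4.3
- s = 18: k = 1 + 0.96/(4.29 × 0.174) = 2.3

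The article gives no event rates, so k is unknown.

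**Relapse-related events outside the window.** If remission takes 1 to 4 weeks (assumption), the usual relapse course lasts 7 to 10 weeks. The 30-day tail covers 4.29/7 = 61% to 4.29/10 = 43% of it. For completers the window ends at week 28 + 4.29 = 32.3. With s = 4, the share of first relapses within 12 months that occur after that is [exp(−28.29λ) − (1 − p)]/p. This is (0.442 − 0.25)/0.75 = 26% on placebo and (0.703 − 0.55)/0.45 = 34% on levamisole.

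**The 30-day rule beside Table 1.** For a completer the two agree: week 36 is the first visit after week 32.3. For a child who stops for good at week 12, the definition ends at week 12 + 4.29 = 16.3, yet Table 1 asks for adverse events at weeks 20, 28 and 36. The article does not say which governs.

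**The case against.** Several points against the concern stand and limit it.

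- **Relapse need not close the window.** A reader might infer that every relapse ends counting for good. The article does not establish this: the stop is worded as possibly temporary and nothing is said about resumption. If drug is resumed, the window stays open and the gap shrinks towards zero.
- **A relapse stop need not count as a discontinuation.** A reader might infer that the discontinuation endpoint simply repeats efficacy. Box 2 does not define the term, and its definition may properly sit in the full protocol or analysis plan.
- **Relapse-related steroid toxicity is truncated, not missed.** The first 30 days after a stop are counted. Cumulative steroid dose and relapse rate are followed for 2 years, physical examination continues, hospitalisation days and quality of life are endpoints, and a patient diary records adverse events. Dose measures exposure rather than harm, however, so the truncation remains.
- **The direction is not certain.** More placebo children would contribute the 30 days of intensified steroid treatment after a relapse, and a high enough event rate there would cancel or reverse the excess on levamisole.
- **Table 1 may govern.** If every child's events count to week 36, the imbalance disappears. The 30-day rule and the fixed visits cannot both apply to an early stopper.
- **The convention is common.** On-treatment plus 30 days is a familiar safety window. It serves less well where the efficacy outcome itself ends treatment and raw counts are compared.

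None of this settles the end date for early stoppers, which the article leaves in conflict.

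**Conclusion.** The concern holds in a conditional form. As written, the length of safety observation can depend on the primary outcome, and the endpoint is a raw count. At the design relapse rates, with no resumption after relapse and equal event rates throughout, levamisole would show about 4% to 16% more adverse events from observation time alone. The upper figure assumes relapses from week 4 at a constant hazard, the lower none before week 18. The gap approaches zero with resumption and vanishes if Table 1 governs. It would be offset if the event rate after a relapse stop were about 2.3 to 4.3 times that elsewhere. The document does not show that both safety comparisons are biased.

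Two things hold whatever the assumptions. The 30-day rule and Table 1 disagree for children who stop early. Events late in a relapse steroid course, or from relapses after about week 32 in children who finish study drug on schedule, fall outside the definition. If relapse stops are counted as discontinuations, about 23 against 12 (or 15 against 7) of 46 would arise from relapse alone, so that total would partly repeat the efficacy result.

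**What to change.** 1. Reconcile the adverse-event definition in Intervention with Table 1. Collect (serious) adverse events in every randomised child to one fixed time, whatever the study drug status. Week 36 is already ticked; week 52 needs only two more ticks, at the existing week 44 and 52 visits, and would capture events up to the time of the primary endpoint.
2. Compare events per child-time between arms, and show the on-drug-plus-30-days window as a second table.
3. State whether study drug may be resumed after a relapse stop under the existing rules, so that the end of the on-drug window is defined.
4. Report treatment discontinuations by reason, with relapse stops on their own line. A competing-risk analysis of the other stops is optional.

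**Cost.** There would be slightly more event reporting after study drug has stopped, and a few lines of analysis. Because recruitment has begun, a protocol amendment is also needed, with ethics and authority review if it is judged substantial. None of this changes how any child is treated.

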### Investigational medicinal product

Levamisole (Elmisol) and placebo tablets are produced, according to Good Manufacturing Practices, and supplied by ACE Pharmaceuticals B.V., Zeewolde, The Netherlands. Elmisol is registered as an orphan drug (European Medicines Agency, 2005). Currently, it is prescribed off-label for the treatment of SSNS in children. Tablets are available in four strengths: 5, 10, 25 and 50 mg. The placebo tablets will match the active drug tablets in appearance, taste and weight, and will only contain pharmacologically inactive substances. Bottles with tablets will be sent to the patient by the Academic Medical Center (AMC) clinical pharmacy.

### Questionnaires

To investigate the effect of INS on the HRQoL, psychosocial adaptation, school performance and parental distress, parents and patients (if 8 years and older) will be asked to complete HRQoL questionnaires at five different time points: at first presentation, at 4 weeks after presentation (prednisolone only), at 28 weeks after presentation (after study treatment), at 1 year after presentation (primary endpoint) and at 2 years after presentation (end of study). Different validated HRQoL questionnaires will be used (table 2).^13–15^ The Paediatric Quality of Life Inventory Generic Scale 4.0 consists of both self and proxy reports including a broad age range (2–18 years).^13^ Norm scores for a Dutch healthy norm population and for children with other chronic illnesses (eg, asthma) are available.^16 17^ The Strength and Difficulties Questionnaire (SDQ) assesses the psychosocial adjustment of children and adolescents.^14 18 19^ Lastly, the Distress Thermometer for Parents is a brief screening instrument to identify distress and everyday problems in parents of children with a chronic condition.^15 20^ In addition, general questionnaires regarding demographics, medication and compliance will be sent to all parents and/or children. KLIK (*Dutch*: Kwaliteit van Leven In Kaart) is a web-based platform for HRQoL questionnaires, developed by the Psychosocial Department of our hospital and used by over 10 000 patients and 400 healthcare professionals.^21^ It is used for both daily clinical care and research in a broad paediatric field. In this study, the KLIK website (www.hetklikt.nu) will be used for filling out the questionnaires; it will only be used for research purposes. In contrast to daily clinical use, the patient will not receive feedback by his or her treating physician. After registration on the website, parents and, if applicable, patients of 8 years and older receive a reminder by email 7 days prior to their next visit.

**Table 2 T2:** Overview of quality of life questionnaires used per age range. At each time point, all questionnaires are provided

Age range	2–3 years	4 years	5–7 years	8–10 years	11–12 years	13–16 years
	Parent about parent	Parent about parent	Parent about parent	Parent about parent	Parent about parent	Parent about parent
Sociodemographics*	General	General	General	General	General	General
Parental distress†	DT-P	DT-P	DT-P	DT-P	DT-P	DT-P

	Parent about child	Parent about child	Parent about child	Parent about child	Parent about child	Parent about child
QOL child	PedsQL (2–4)	PedsQL (2–4)	PedsQL (5–7)			
Psychosocial adjustment	SDQ (2–3)	SDQ (4–18)	SDQ (4–18)	SDQ (4–18)	SDQ (4–18)	SDQ (4–18)
Problems with medication and compliance	Medication and compliance	Medication and compliance	Medication and compliance			
School		School	School			

	Child	Child	Child	Child	Child	Child
QOL child				PedsQL (8–12)	PedsQL (8–12)	PedsQL (13–18)
Psychosocial adjustment					SDQ (11–16)	SDQ (11–16)
Problem with medication and compliance				Medication and compliance	Medication and compliance	Medication and compliance
School				School	School	School

*Once at baseline.

†By both parents, if applicable.

DT-P, Distress Thermometer for Parents; PedsQL, Paediatric Quality of Life Inventory; QOL, quality of life; SDQ, Strengths and Difficulties Questionnaire.

